**Interventions**					
	Qigong		✓	✓	
	Pain management survey		✓	✓	
**Assessments**					
	Fitbit Charge 6 smartwatch	✓	✓	✓	✓
	EMA^a^ surveys	✓	✓	✓	
	Zoom questionnaires	✓	✓		✓
	Weekly calls		✓		
	Monthly calls			✓	

^a^EMA: ecological momentary assessment.

### Participants and Recruitment

For aim 1, the inclusion criteria are 40 SCI stakeholders, which can be adults with SCI, caregivers, health care professionals, or other stakeholders who have experience with caring for adults with SCI, especially those with health disparities.

The inclusion criteria for aim 2 are persons aged 18+ years, 40 participants with an incomplete or complete SCI of ≥1 year, medically stable, and with ≥4/10 for highest neuropathic pain intensity level on the Numeric Pain Rating Scale [31]; willing to participate in a remote Qigong intervention (from any location with internet connection), fluent in English or Spanish, access to the internet and a computer, iPad, or smartphone. We aim to recruit at least 50% (n=20) of adults with health disparities (ie, racial or ethnic minorities, Veterans, or living in rural, underserved areas).

The exclusion criteria are uncontrolled seizure disorder, cognitive impairment or communicative disability (eg, due to brain injury) preventing them from following directions or from learning, ventilator dependency, major medical complications, pressure ulcers hindering prolonged sitting or lying down, (planning to become) pregnant or planning a major surgery during the study (given the study duration, regular Qigong practice or surveys, and frequent check-ins), regular Tai Chi or Qigong practice in the past 6 months (3×/week or more) or currently engaged in other rehabilitation programs that would influence outcomes.

We estimate recruiting 30%-40% (12-16/40) of adults with complete versus 60%-70% (24-28/40) incomplete SCI based on our prior data in SCI and on reported statistics of 23% (9/40) complete paraplegia, 15% complete tetraplegia (6/40), 22% incomplete paraplegia (9/40), and 40% incomplete tetraplegia (16/40) [32].

We will recruit from all clinical site partners within the Minnesota Regional SCI Model System, which includes hospitals, clinics, rehabilitation centers, long-term care facilities, and nursing homes in the Twin Cities and Mayo Clinic in Rochester. Specifically in the Twin Cities, we have collaborations within the Veterans Affairs (Minnesota), including the Minnesota Paralyzed Veterans, University of Minnesota Medical Center, University of Minnesota Health (M Health) Fairview, Regions Hospital, Courage Kenny Rehabilitation Institute, and Minnesota SCI associations. Health care providers will provide information to potential participants and post fliers.

M Health Fairview has a recruitment system in place where letters are sent from their system directly to patients with SCI and neuropathic pain. Patients who are interested in participating can contact the researchers. We also collaborate with the SCI patient advocacy association United to Fight Paralysis.

In 2019, a total of 530 adults with new SCI were treated in the Twin Cities clinics, with 311 receiving outpatient therapy in rehabilitation centers. In 2022, a total of 285 adults with SCI received annual evaluations, along with other visits to the Minneapolis Veterans Affairs Medical Center, totaling about 550 unique visits and 7500 encounters.

Based on the population of Hispanic origin (8.5 million) in Texas [33], and an SCI incidence rate of 54 cases per million [32,34], we expect that there are about 432 new cases of SCI per year in Texas. Our UTRGV team has committed to assisting with recruitment and retention strategies in minority groups in the Rio Grande Valley, with a 98% Hispanic population, and where almost 30% live in poverty [35,36].

There are about 200-300 adults with SCI in the Rio Grande Valley: 75-100 treated at UTRGV and >250 treated at the Rehabilitation Institute at the Doctors of the Hospital Renaissance in the Rio Grande Valley. The UTRGV team will involve Hispanic community leaders, adults with SCI, their families, caregivers, and SCI health care workers.

We will also recruit nationwide through regional and national SCI or professional organizations and will post fliers and information on relevant websites and social media. We have successfully recruited participants nationwide in our preliminary remotely delivered Qigong study [14]. Given the prevalence of 308,620 adults with SCI in the United States (with 69% neuropathic pain prevalence) and given our completely remote clinical trial part of the proposal, we have many opportunities to recruit 40 participants with SCI-related neuropathic pain (as well as 40 SCI stakeholders for aim 1), even with an estimated 30% screening failures based on inclusion and exclusion criteria.

We have also taken into account patient and public involvement. Literature shows that adults with SCI, their families, and caregivers who have experience with mind and body approaches are more likely to recommend such approaches compared to health care professionals [37]. Therefore, we have 3 SCI consultants on the team. Our Latina consultant in Minnesota will facilitate communication between the research group and the Hispanic community in Minnesota, whereas the SCI consultant in South Texas will do the same for the Rio Grande Valley region, by educating the team and facilitating the cultural acceptability of Qigong, pain management surveys, and the study protocol (including assessments) for the Hispanic community. Our Veteran SCI consultant has given input on the feasibility of Qigong practice for adults with paraplegia and tetraplegia, and the duration of remote clinical assessments. All SCI consultants will provide input throughout the study and be invited to attend quarterly meetings, where they will be informed about the progress of the study.

### Interventions

Two active interventions are proposed, with different “active ingredients.” More information about the interventions is given below.

The Qigong introduction class will be taught over Zoom by a Spring Forest Qigong-certified instructor. Then, participants will practice Qigong at least 3 times per week for 12 weeks with the “Five Element Healing Movements” online video with streaming access from any computer, iPad, or smartphone device, so participants can practice at home or any location with an internet connection. More details about the content of the Qigong practice can be found in our published protocol paper of the Qigong pilot study in adults with SCI-related neuropathic pain [25]. Participants log in with a unique study identification number and password onto the Spring Forest Qigong website to access the video and practice at least 3 times per week for 45 minutes per session. Their practice (time and duration of access) will be logged automatically and sent to the principal investigator ([name]), who is level 5 (of 5 levels) in the Spring Forest Qigong curriculum, and a certified practice group leader.

Once a month, the Spring Forest Qigong-certified instructor will do a Qigong session 1:1 with each participant over Zoom to monitor their practice, address questions, demonstrate movements, and give guidance as needed to ensure quality control of the practice. We will use the recording option on the Zoom platform, and the video will be stored on our server, called the University of Minnesota secure box.

The active comparison group will receive a daily text or email message (depending on the choice of the participant) linking them to a 2-minute online Qualtrics survey to answer questions related to their pain intensity level, medications taken that day, activities that helped or hindered the pain, and free text on what they did that day that mattered to them. There are no educational or lifestyle advice components, and they will not receive any guidance on any of the active ingredients given in Qigong (ie, breathing, meditation, and meditative movements). Pain management has been examined through an app in multicenter trials and feasibility studies and is being used in large health care systems in Canada [38].

We will organize weekly (during the intervention) and monthly check-ins (during the 6-month follow-up) to encourage adherence. The Qigong group will also receive a 1:1 session per month with the Qigong instructor to verify the quality of practice and address any questions. The research staff will contact the participant if the pain management surveys are not completed 2 days in a row.

All participants will continue their prescribed or over-the-counter pain medication and maintain their regular standard-of-care health care appointments. However, any current regular (3 times per week or more) mind and body practices, such as Tai Chi, Qigong, or any rehabilitation programs that would influence outcomes, will not be permitted.

The study does not provide compensation for research-related injuries or unexpected urgent care.

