Behavioral assessments will be acquired remotely at 3 time points: at baseline, after the 12-week interventions, and at the 6-month follow-up. This 6-month follow-up period will assess behavioral changes and the sustainability of Qigong practice adherence or pain management survey adherence in daily life. In our prior study, participants enjoyed continuing Qigong practice because it helped them manage their pain [14]. Both groups will receive weekly calls during the 12-week intervention period and monthly calls during the 6-month follow-up to assess neuropathic pain (primary outcome) and neuropathic pain medication, including opioid use, adherence to Qigong practice or the pain management surveys, adverse events, illnesses, and use of health care services. Qualitative information will be collected about their adherence, adverse outcomes, if any, perceptions, effects, and satisfaction with the Qigong practice or pain management surveys. Ecological momentary assessments (EMAs), consisting of 2-minute Qualtrics surveys are delivered 4 times per day for 3 weeks at baseline, during the last 3 weeks of the 12-week interventions, and during the last 3 weeks of the 6-month follow-up to identify feasibility of data that can explore causal relationships between variables of mood, activity, sleep, and so on, and neuropathic pain to understand in each individual which variables increase or decrease neuropathic pain. Objective data on sleep, stress, and other information will be collected continuously with the Fitbit Charge 6 wrist device. Fitbit data will also be time-synchronized with EMA data at those 3 time points to evaluate the feasibility of data that can explore causal relationships between physiological data, behavioral data, and neuropathic pain. The study is offered in English and Spanish to increase accessibility to those for whom English may be a barrier.

The SPIRIT (Standard Protocol Items: Recommendations for Interventional Trials) 2013 checklist with recommended items to address in a clinical trial protocol and related documents (Multimedia Appendix 1) and the SPIRIT template of recommended content for the schedule of enrollment, interventions, and assessments (Table 1) are included.

**Table 1 table1:** Scheduling of enrollment, intervention, and assessments.

		Study period			
Timepoint		Enrollment	12-week intervention	6-month follow-up	Close-out
**Enrollment**		Week 0	Week 1-12	Week 13-37	Week 38
	Eligibility screen	✓			
	Informed consent	✓			

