Feasibility of adhering to the collection of quantitative measures	% Adherence in completing all assessments during the study and in the monthly follow-up phase until 6 months postintervention. % Adherence to wearing the Fitbit Charge 6 smartwatch and sending the data through their Fitbit app on their smartphone.	Feasibility is ‘excellent’ when none of the Zoom questionnaires, EMA^b^ surveys, or weekly and monthly check-ins are fully missing in >25% of the participants. Excellent adherence: data from the Fitbit app at least 70% of the time and wearing the Fitbit Charge 6 at least 5 out of 7 days/week for at least 7 hours/day (≥80% excellent; ≥70% good).
Program satisfaction	3-item Client Satisfaction Scale [47]. Ask about their intent (and frequency) to continue the Qigong practice or pain management surveys after the 12-week intervention program.	Excellent satisfaction if ≥75% of the participants score above the scale midpoint; and good if ≥70%. Our benchmark is ≥70% of the participants intend to continue the Qigong practice or pain management surveys after 12 weeks.
Program safety	Assess adverse events (IRB^c^+GCP^d^ reporting guidelines) and report adverse events via ACTTION^e^ recommendations [48,49].	Excellent safety: no study-related adverse events; good if there are minimal and mild adverse events (eg, muscle soreness) linked to Qigong practice in max 10% of participants, or any adverse events with the pain management surveys. We will ask about adverse events during the weekly and monthly check-in calls.

^a^SCI: spinal cord injury.

^b^EMA: ecological momentary assessment.

^c^IRB: Institutional Review Board.

^d^GCP: Good Clinical Practice.

^e^ACTTION: Analgesic, Anesthetic, and Addiction Clinical Trial Translations, Innovations, Opportunities, and Networks.

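### The 6-month follow-up is meant to show whether adherence lasts in everyday life, but the study goes on encouraging adherence throughout it, so the rate is supported continuation and should be labelled so

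*Protocol article*

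**What the plan says.** **Purpose of the follow-up** (Overall Study Design): "This 6-month follow-up period will assess behavioral changes and the sustainability of Qigong practice adherence or pain management survey adherence in daily life".

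**Purpose of the calls.** Overall Study Design presents them as assessment: "Both groups will receive weekly calls during the 12-week intervention period and monthly calls during the 6-month follow-up to assess neuropathic pain". The same sentence lists adherence to Qigong or to the surveys among the items recorded. Interventions gives them another aim: "We will organize weekly (during the intervention) and monthly check-ins (during the 6-month follow-up) to encourage adherence".

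**What runs in weeks 13-37.** In Table 1, the Qigong row and the "Pain management survey" row are each ticked under the 12-week intervention and again under the 6-month follow-up. The Interventions text, by contrast, sets Qigong practice for 12 weeks. In Table 2, the satisfaction row treats going on afterwards as the participant's intention: "Our benchmark is ≥70% of the participants intend to continue the Qigong practice or pain management surveys after 12 weeks".

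**Arm-specific support** (Interventions). For the survey arm: "The active comparison group will receive a daily text or email message", and "The research staff will contact the participant if the pain management surveys are not completed 2 days in a row". For the Qigong arm: "The Qigong group will also receive a 1:1 session per month with the Qigong instructor". None of these three sentences says when the support stops. Study Setting puts the number of one-to-one instructor sessions at three.

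**The concern.** A sustainability rate is useful because it shows what people do once the study stops pushing them. Here the calls that record adherence are also meant to raise it, and they continue through the whole period in which sustainability is to be judged. A rate reported under the stated objective would be read as persistence in ordinary life, when it was in fact obtained under regular staff contact.

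The schedule adds a second difficulty. If Table 1 governs, weeks 13-37 are continued intervention, and a missed session or survey is non-adherence. If the 12-week description governs, the same weeks are voluntary, and a missed session is simply a choice. The same log data would answer different questions under the two readings. What is at stake is the interpretation of the follow-up adherence rate and of any comparison of that rate between arms. Sample size and error rates are not affected.

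**Working it through.** The plan states no figure for follow-up adherence, so there is nothing to reproduce. The check compares the passages and counts contacts.

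**1. Purpose against procedure.** The objective concerns adherence in everyday life. The procedure holds monthly calls in the same period with the declared aim of encouraging adherence. Both statements are explicit, so the conclusion that follow-up adherence is encouraged adherence needs no inference.

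**2. Schedule against text.** Table 1 continues both interventions in follow-up. The sentence on the calls itself distinguishes an intervention period from a follow-up period, the Qigong practice period is given as 12 weeks, and Table 2 asks about intent to continue. The document does not say whether weeks 13-37 are prescribed or voluntary.

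**3. Length of follow-up** (Table 1): 37 − 13 + 1 = 25 weeks; 25 × 7 = 175 days. Monthly calls over six months: about 6 per arm.

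**4. Does support differ by arm?** Count staff contacts in weeks 13-37. The daily survey link is left out because it is how the survey is delivered; without it there is nothing to complete.

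- Qigong arm: about 6 calls if the one-to-one sessions are the three in Study Setting, which at one per month fill the 12 weeks. If the monthly sessions in Interventions run on, 6 + 6 = about 12.
- Survey arm: about 6 calls if the two-day contact rule ends at week 12. If it runs on, add the expected number of two-day misses. Assume independent days with daily miss probability q, and restart the count after each contact. The mean waiting time to two consecutive misses is then (1 + q)/q² days, so the expected number of contacts is 175 × q²/(1 + q).

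| q (assumed) | Two-day contacts | Total with 6 calls |
|---|---|---|
| 0.10 | 175 × 0.01/1.10 = 1.6 | 7.6 |
| 0.20 | 175 × 0.04/1.20 = 5.8 | 11.8 |
| 2/7 (exactly 5 of 7 days completed) | 175 × 0.0816/1.2857 = 11.1 | 17.1 |

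The survey arm thus ranges from about 6 to 17 contacts and the Qigong arm from about 6 to 12. Depending on which supports continue and on q, the survey arm has more (17.1 against 12, or 11.8 against 6), about the same (11.8 against 12), or fewer (7.6 or 6 against 12). The document does not fix the direction.

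**5. Contact counts are not effects.** Nothing in the document links a call, a reminder or an instructor session to a change in adherence, so the inflation cannot be sized in either arm.

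**The case against.** The strongest reply is that everyday life need not mean unsupported life. The section that states the sustainability purpose also discloses the monthly calls shortly afterwards, and going from weekly to monthly contact is a visible taper. Continuation under light contact is a legitimate quantity, and video access and Qualtrics completion are logged, so it can be measured. Asking about intent to continue is a satisfaction item and is compatible with leaving the video and surveys available to see what people do. All of this stands, and it is why the remedy is a relabelled objective and not an abandoned one. It does not remove the stated aim of encouraging adherence, or the disagreement between Table 1 and the 12-week description.

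Three stronger readings are tempting, and the document does not support them.

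- *The survey arm is more heavily supported.* A reader may infer this because the two-day rule has no end date and Qigong has no missed-session counterpart. The monthly instructor session in the same paragraph of Interventions has no end date either. If the three sessions in Study Setting confine that support to 12 weeks, the two-day rule may be confined too.
- *The two-day rule protects the 5-of-7-days benchmark in Table 2.* It does so only in part. Three non-consecutive misses in a week leave 4 of 7 days completed and trigger no contact.
- *The phase II design will rest on an inflated persistence rate.* Neither the Aim 2 targets nor Table 2 sets a separate benchmark for persistence in follow-up, and a later trial with similar calls would want adherence under similar calls.

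**Conclusion.** The point holds for the meaning of the follow-up rate. As written, the trial will measure adherence under about 6 monthly encouragement calls per arm over 25 weeks, with both interventions scheduled to continue, and this should not be reported as unsupported sustainability. That conclusion rests on explicit text alone.

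That support differs between arms is a possibility and not a finding. It depends on whether the two-day contact and the one-to-one sessions run past week 12, and the article leaves this unsettled. The contact counts assume six calls, independent days and illustrative miss rates; they serve only to show that the direction is open. The amount by which encouragement raises adherence cannot be derived. Nor does the document support saying that follow-up adherence is uninterpretable: continuation under monthly contact can be estimated from the logs. The correction is worth making because it changes what the trial can claim, at little cost.

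**What to change.** 1. In Overall Study Design, restate the follow-up objective as continuation of Qigong practice or survey completion under monthly study contact.
2. Reconcile Table 1 with Study Setting, Interventions and the satisfaction row of Table 2. State for each arm whether weeks 13-37 are continued intervention or voluntary continuation, and whether the two-day missed-survey contact and the one-to-one sessions run after week 12.
3. Report follow-up adherence from the existing video-access and Qualtrics logs, by month and arm, with the number of staff contacts per arm alongside.
4. Optionally, for participants not yet past week 12, make the monthly calls data collection only and end the two-day contact at week 12, reporting these participants separately from those followed under the present rules.

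Items 1 to 3 leave contact with participants unchanged. They cost a less favourable label for the rate and a little more tabulation. Item 4 is a real trade-off. Ethical Considerations requires IRB approval of every amendment and, if applicable, a new signed consent form. The Results section reports 36 participants recruited to aim 2 by September 2025, 8 of whom had dropped out, so only 40 − 36 = 4 remained to be recruited. The number not yet past week 12 is not given. The change would split a small sample into two contact regimes, and the survey arm would still receive its daily link. The first three items are enough to correct the claim.

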### Demographic and Clinical Outcomes

Four types of remotely delivered assessments are used in this study: (1) demographic and SCI-related medical information, (2) feasibility benchmarks, (3) patient-reported outcome measures (questionnaires and EMA surveys), and (4) objective measurements with the commercially available Fitbit Charge 6 smartwatch.

#### Demographic, SCI-Specific Data, and Screening

We will collect National Institute of Neurological Disorders and Stroke – Common Data Elements (NINDS-CDE) SCI-demographic, SCI-relevant general health, and SCI-specific data. We will screen participants with the Mini-Mental State Examination-short version (cutoff score <13/16) [39], and test their ability to perform kinesthetic motor imagery with the Kinesthetic and Visual Imagery Questionnaire (cutoff score <15/25 points) [40]. While imagining body parts affected by SCI may be difficult for participants at baseline, overall impaired kinesthetic imagery is rare: no adult with SCI scored below the cutoff score in our prior studies [14,41].

#### Feasibility Benchmarks

Our feasibility markers are consistent with models and guidelines for intervention development (Table 2) [29,42]. Based on prior publications [43-46], we will assess the following a priori feasibility markers.

**Table 2 table2:** Feasibility benchmarks.

	Feasibility item and details	Benchmark (go/no-go criteria)
Recruitment and enrollment	Assess recruitment rates (screens and enrollment per trimester, sex, and racial outcomes). Evaluate the recruitment rate for complete and incomplete SCI^a^. We aim to recruit 40 participants between mid-year 1 and year 2.	The proportion of potential participants contacted who agreed to participate: 80% is excellent and 70% good. Ratio of complete/incomplete SCI. We estimate recruitment of 30%-40% of adults with complete, 60%-70% with incomplete SCI. Reasons for (not) participating and information collected during focus groups or interviews will help delineate facilitators and barriers to participation, including computer or internet access.
Feasibility and acceptability of the study design	Attrition rates in the Qigong or pain management survey groups.	Proportion of people withdrawing from the interventions. Dropout due to unrelated reasons will count as part of the general attrition. A proportion of 90% is excellent, and 80% good.
Feasibility, adherence, and acceptability of the Qigong practice	Assess intervention adherence, average Qigong practice, at least 3×/week (123 minutes), pain management surveys (daily), and satisfaction with the Qigong practice or pain management surveys. Identify facilitators and barriers to practicing Qigong at home or completing the pain management surveys.	Weekly and monthly check-ins (reporting minutes/week of practice) to identify facilitators and barriers to pain management surveys or practicing Qigong. The Qualtrics website (for pain management surveys) or Spring Forest Qigong website (for Qigong practice) logs time and duration of video access. A Spring Forest Qigong-certified instructor will do a 1:1 Qigong session with each participant via Zoom monthly for quality control and to give guidance. Feasibility: Excellent: >80% participants practice at least 2×/week; good ≥70%. For the pain management survey: completion of surveys at least 5 out of 7 days. Dropout due to lack of interest will be counted as general attrition: 10% dropout is excellent, 20% is good.
Feasibility of adhering to the collection of quantitative measures	% Adherence in completing all assessments during the study and in the monthly follow-up phase until 6 months postintervention. % Adherence to wearing the Fitbit Charge 6 smartwatch and sending the data through their Fitbit app on their smartphone.	Feasibility is ‘excellent’ when none of the Zoom questionnaires, EMA^b^ surveys, or weekly and monthly check-ins are fully missing in >25% of the participants. Excellent adherence: data from the Fitbit app at least 70% of the time and wearing the Fitbit Charge 6 at least 5 out of 7 days/week for at least 7 hours/day (≥80% excellent; ≥70% good).
Program satisfaction	3-item Client Satisfaction Scale [47]. Ask about their intent (and frequency) to continue the Qigong practice or pain management surveys after the 12-week intervention program.	Excellent satisfaction if ≥75% of the participants score above the scale midpoint; and good if ≥70%. Our benchmark is ≥70% of the participants intend to continue the Qigong practice or pain management surveys after 12 weeks.
Program safety	Assess adverse events (IRB^c^+GCP^d^ reporting guidelines) and report adverse events via ACTTION^e^ recommendations [48,49].	Excellent safety: no study-related adverse events; good if there are minimal and mild adverse events (eg, muscle soreness) linked to Qigong practice in max 10% of participants, or any adverse events with the pain management surveys. We will ask about adverse events during the weekly and monthly check-in calls.

^a^SCI: spinal cord injury.

^b^EMA: ecological momentary assessment.

^c^IRB: Institutional Review Board.

^d^GCP: Good Clinical Practice.

^e^ACTTION: Analgesic, Anesthetic, and Addiction Clinical Trial Translations, Innovations, Opportunities, and Networks.

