### Statistical Analyses

#### Sample Size Calculation

We plan on recruiting 40 SCI stakeholders (aim 1) and 40 adults with SCI-related neuropathic pain (aim 2). Stakeholders not only include adults with SCI but also caregivers and health care professionals and any other stakeholder related to adults with SCI.

Aim 1 requires a qualitative analysis, and thus, power analysis is not calculated.

The sample size for aim 2 of 40 adults with SCI-related neuropathic pain is based on our estimated accrual and enrollment rates from our prior studies on related research. Due to the nature of a feasibility study, power calculations were not conducted. With N=40, we will be able to estimate a rate for the feasibility endpoints, for example, the dropout rate, of 80% with the margin of error of the 95% CI controlled at ±10%. Based on prior literature, the sample size is sufficient to provide reliable estimates of the mean and SD of pain (primary outcome) and other outcomes, to determine the required sample size for future large efficiency studies.

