## Results

We report protocol version 2 and do not anticipate any further changes until trial completion. We registered and posted the trial on ClinicalTrial.gov registration (NCT06140355) on November 20, 2023. The first participant was recruited on August 20, 2024. Study completion is estimated on January 31, 2027. At this time (September 2025), 20 participants have been recruited for aim 1 (no dropouts) and 36 participants were recruited for aim 2, with 8 participants dropping out of the study.

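### Table 2's attrition benchmark runs backwards: it measures the proportion withdrawing, yet rates 90% as excellent and 80% as good, the reverse of the next row

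*Protocol article*

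**What the plan says.** All references are to the protocol article.

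- **Table 2, attrition row** (study design feasibility and acceptability). The item is "Attrition rates in the Qigong or pain management survey groups". The benchmark cell gives the measure as "Proportion of people withdrawing from the interventions", adds "Dropout due to unrelated reasons will count as part of the general attrition", and ends with "A proportion of 90% is excellent, and 80% good". The column heading marks these entries as go/no-go criteria.
- **Table 2, next row** (Qigong practice adherence). After the adherence thresholds it states: "Dropout due to lack of interest will be counted as general attrition: 10% dropout is excellent, 20% is good".
- **Sample Size Calculation.** The precision statement for N=40 takes as its illustration "for example, the dropout rate, of 80" per cent.
- **Results.** As of September 2025, "36 participants were recruited for aim 2, with 8 participants dropping out of the study". Completion is estimated for January 2027.
- **Introduction, Background.** The earlier pilot is reported in retention terms: 18 of 21, given as 86%.

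**The concern.** The attrition row names withdrawal as the quantity and nothing in the cell switches to retention or completion. The two figures that follow therefore apply to withdrawal, and a higher withdrawal rate earns a better grade. The next row grades dropout the other way round. Both rows say that the dropout they describe belongs to general attrition, so the same quantity is scored twice, in opposite directions.

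At stake is whether a prespecified benchmark can be read at all. Attrition in both groups is one of the listed aim 2 targets, and the article presents the benchmarks as set a priori to judge whether a larger trial should follow. The dropout reported so far lies near the 20% line, so the direction and scope of the rule should be beyond dispute before the final figures are in.

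**Working it through.** The 90% and 80% figures are stated thresholds with no formula behind them, so there is nothing to reproduce. The check is one of consistency.

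**1. The two rules as counts out of the planned 40.**

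| Rule | Excellent | Good |
|---|---|---|
| Attrition row as written (proportion withdrawing) | 0.90 × 40 = 36 withdraw | 0.80 × 40 = 32 withdraw |
| Next row (dropout) | 0.10 × 40 = 4 drop out | 0.20 × 40 = 8 drop out |
| Attrition row read as retention | 36 retained, so 4 lost | 32 retained, so 8 lost |

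The second and third lines agree exactly: 1 − 0.90 = 0.10 and 1 − 0.80 = 0.20. The 90%/80% pair is therefore the 10%/20% rule expressed as retention, placed beside the word for its opposite.

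**2. The pilot.** 3/21 = 14.3% dropout, or 18/21 = 85.7% retained. This is good under the next row and under the retention reading. Under the attrition row as written, 14.3% lies far below both figures and the row gives no sensible grade.

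**3. The count in Results.** Treating recruited as randomised, which the article does not state:

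- Dropout: 8/36 = 22.2% (exact 95% CI 10.1% to 39.2%). Retention: 28/36 = 77.8%.
- Under the 20% dropout rule, 22.2% is just outside good. Under the 80% retention reading, 77.8% is just outside good. The two give the same answer, as complements must.
- If enrolment reaches 40 with no further loss: 8/40 = 20.0%, exactly on the line. With one more loss: 9/40 = 22.5%.

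**4. Scope.** The attrition row brings in dropout for unrelated reasons and the next row brings in dropout for lack of interest. If the 10%/20% rule were applied to lack-of-interest dropouts alone, seven of the eight would give 7/36 = 19.4%, within good; all eight give 22.2%, outside it. The article does not report reasons for the eight dropouts, so this only shows that the two rows need one shared measure.

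**5. The sample-size sentence.** The variance term p(1 − p) is 0.8 × 0.2 = 0.16 whether 80% is dropout or retention, so the direction has no effect on the margin of error.

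**The case against.** The strongest reply is that nobody would apply the row literally. The next row prints the right direction with exactly complementary figures, and the pilot was reported as retention. This stands. The intended meaning is recoverable, and the correction moves no cut-off.

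A reader might go further and infer that the trial has already missed its attrition benchmark, or that a threshold corrected after the 8 of 36 became known can no longer support a prespecified verdict. The documents support neither. The count is interim. It concerns people recruited who dropped out of the study, and is not shown to be randomised participants withdrawing from the interventions; nor is it split by group. The 10%/20% rule is already in the published text, so a corrected row can rest on wording that predates the final result.

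It is also fair to say that the sample-size sentence is weak evidence of a second reversal. Its 80% can attach to a rate for the feasibility endpoints in general, with the dropout rate as a loose example. It is a reason to tidy the wording and no more.

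Finally, a correction that deleted the next row's threshold, or built a new definition with new tiers, would remove the best evidence of prior intent and invite the charge of a post hoc change. That limits what the fix should do. None of this removes the contradiction: a go/no-go entry is wrong as printed, and the cell itself contains nothing that puts it right.

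**Conclusion.** The point holds as a direction error in a stated decision threshold. As written, the attrition row rates 36 of 40 withdrawals as excellent and 32 of 40 as good, where the next row sets 4 and 8. Read as retention, the two rows agree exactly.

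The size of the problem is limited. No cut-off changes, and no sensible reading of the direction alters how the reported dropout would be graded. It is still worth correcting now, because the reported 22.2% is close to the 20% line (on the assumption that recruited equals randomised) and because the two rows split general attrition by reason without saying that it is scored once.

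**What to change.** 1. **Attrition row of Table 2.** Restate the measure as retention, for example: proportion of participants retained, meaning not withdrawn for any reason, with unrelated reasons and lack of interest both counted as withdrawal; 90% or more is excellent and 80% or more is good, equivalent to dropout of at most 10% and at most 20%.
2. **Adherence row of Table 2.** Keep the 10%/20% figures, but make the sentence refer to the measure in the attrition row, so that general attrition is scored once.
3. **Sample Size Calculation.** Change the example to a retention rate of 80%, for consistency only.
4. **Record of the change.** Date it, cite the existing 10%/20% text as its prespecified basis, and disclose that 8 of 36 recruited participants (22.2%) had dropped out by September 2025. Say whether those 36 had all been randomised.

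The cost is a few lines of text, plus a protocol amendment if the full protocol carries the same wording. The article expects no further changes before trial completion, so the correction has to be made deliberately. No data collection, visit or sample size is affected.
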